### Recruitment {15}

Rheumatologists working in all hospitals in the South-West region of The Netherlands have agreed to inform all eligible patients with CSA on the TREAT EARLIER trial and, with the consent of the patient, to transfer the patients’ contact details to the study doctor in the LUMC (Fig. 3). The study doctor is then responsible for the screening process.

It is known from our observational cohort data that the period of CSA with subclinical inflammation is sometimes weeks, often months, and infrequently years [14]. To prevent that patients already progress to clinical arthritis before inclusion in the trial, the logistic of screening will be organized as time-efficient and patient-friendly as possible. This means, among others, that the MRI will be scored directly after it is made. Both readers independently send their MRI scoring results to the study doctor, who compares the results with MRI data of the reference population as described in supplementary file 4. The result (positive or negativity) of the screening MRI will be communicated to the patient and if the patients prefer, and—after informed written consent—randomization can take place on the same day as the screening MRI is performed (Fig. 2).

## Assignment of interventions: allocation and blinding

### Sequence generation {16a}, concealment mechanism {16b}, and implementation {16c}

Participants will be enrolled based on a two-level definition; patients need to have arthralgia that is suspect to progress to RA according to the treating rheumatologist, and patients should have MRI-detected inflammation in the small joints (scored positive by two independent readers; both readers will be unaware of the clinical data and communicate their MRI scoring to the study doctor, without information on the scoring of the other reader). When both criteria are met and informed written consent is obtained, the study doctor, who is only in charge of the trial and does not see patients for routine care, contacts the local pharmacist of the LUMC, who will take care of the randomization, using a block randomization scheme to randomly assign the participants (no stratification will be applied). Once the participants are randomly assigned, both the IM injection and study tablets, available in the pharmacy, will be allocated to the trial participant. IM methylprednisolon or placebo injection and MTX or placebo tablets are distributed and packaged similarly. Every 4 months, study tablets will be in the same way distributed to the trial participant. All participants and staff involved in the conduct of the trial will be blind to treatment allocation throughout the trial.

### Who will be blinded {17a} and procedure for unblinding if needed {17b}

All scientific staff, rheumatologists, research nurses, and participants will remain blind to the treatment allocation. Unblinding will occur if medically necessary. In case the primary endpoint is met, participants will be treated with open-label DMARD therapy according to the routine care and the medication choice is left to the decision of the treating rheumatologist. No unblinding will take place at this time. In case participants will stop the study medication because of side effects at an earlier point in time than the 12-month period, unblinding will not take place as well (in order to prevent expectation bias influencing the treating physicians). The data safety monitoring board (DSMB) receives information blinded to the treatment allocation; however, if required for safety issues, the board can ask the pharmacist to provide them with unblinded data. Otherwise, unblinding will take place when the last study visit after 2 years of follow-up of the last included participant is done, and data quality checks (QCs), as described in the “Data management {19} and confidentiality {27}” section, are performed.

## Data collection and management

### Plans for assessment and collection of outcomes {18a}

Participants will be followed with 4-monthly intervals for 2 years. Whether there is clinically detectable arthritis will be evaluated at all these visits by physical examination of the joints by the treating rheumatologists. In case there is clinically detectable arthritis, an additional visit will be scheduled after 2 weeks to evaluate whether the arthritis is persistent (and not self-limiting) and to verify whether the primary endpoint is met. When this is the case, a visit will take place that includes all assessments, as also measured at 24 months (Fig. 4).

At every visit for 2 years, participants undergo a physical examination and hand function tests. General markers of inflammation (CRP, erythrocyte sedimentation rate), complete blood count (hemoglobin, leukocytes, thrombocytes), and liver and renal function will be measured at every study visit for 2 years. Unilateral MRIs and bilateral X-rays of the hands and feet will be made at study entry; 4, 12, and 24 months; and when the primary endpoint is achieved. Questionnaires will be completed by the participants at every study visit for 24 months.

Data collection forms can be obtained upon request by the study team ([contact]).

Amendment (Protocol version 5, 18-01-2019) includes a deviation of MRI scan. The 1.5-T MRI scanner that is used from 2015 onwards is expected to be technically “end-of-life” after December 2019. It is foreseen that all participants are enrolled, and thus, inclusion MRI scans are completed before that time. The MRI scans made during follow-up can all be obtained either at a 1.5-T or 3-T MRI scanner, depending on the availability at the radiology department. Although in the MSK literature the performance of high-end scanners (different 1.5-T, 3-T scanners) is rather comparable [42–45], we will evaluate the comparability in detecting subclinical joint inflammation of the two scanners that we will use. Therefore, we planned to perform both 1.5-T and 3-T MRIs in up to 30 participants. This will allow us to investigate the comparability of detecting the presence of subclinical inflammation in 360 hand/foot joints, 660 bones, and 540 tendon sheaths (one scan depicts 12 small joints, 22 bones, and 18 tendon sheaths). If the presence of subclinical inflammation at the joint/bone/tendon sheath level will be similarly portrayed with both scanners, no further action will be needed. If the 3-T MRI scanner will be more/less sensitive than the 1.5-T scanner, a correction factor will be included in the analyses on the serial MRIs at the time of analyzing the results on this exploratory endpoint. This correction factor will be determined based on the data of the 30 scans that will be made on both machines. The number of participants needed to scan on both machines is difficult to calculate; however, based on the good comparability observed in the literature, the fact that we will make comparisons at the joint level, but also accounting for the fact that multiple joints/bones/tendon sheaths come from the same participant, we estimate that 30 participants are sufficient.

Both scans will be performed with at least 2 days in between to account for sufficient clearance of intravenous contrast (T1/2 of Dotarem® is 1.4–2.0 h) and with no more than 1 week in between to reduce the impact of biological variation. The US “Food and Drug Administration and the Pharmacovigilance Risk Assessment Committee” have recently concluded that no specific conditions have been linked to gadolinium contrast deposition in the organs [46]. Therefore, it is safe to administer contrast to the patients based on the current literature.

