Tender joint count (TJC-68, range 0–68).Hand function: ability to make a fist (left and right, yes/no), squeeze test (hand, foot, left and right, positive/negative), and grip strength test with a dynamometer (range 0–90).Global assessment (NRS range 0–10).Quality of life: short form-36 (SF-36) (range 0–100), EuroQol 5D-5level (EQ-5D-5L) (per item, range 1–5, and visual analog scale (VAS) range 0–100).Health appraisal: Brief Illness Perception Questionnaire short (B-IPQ) (per item, range 0–10), Rheumatology Attitudes Index (RAI) helplessness subscale (range 5–25).Cost-efficacy measurement by iMTA.Radiographic damage of the hands and feet, Sharp-van der Heijde scores (range 0–448).MRI-detected subclinical inflammation on the unilateral hand and foot, assessed semi-quantitatively using the RAMRIS score, evaluating synovitis (range per joint 0–3), BME (also called osteitis, range per bone 0–3), tenosynovitis (range per tendon sheath 0–3), and erosions (range per bone 0–10) [27, 28]. MRI scoring will be done with known time order and blind to any clinical data. The scores of synovitis, BME, and tenosynovitis are summed as the total MRI inflammation score (variable on the patient level). Total scores will be normalized as described by Sundin et al. [41]. Furthermore, the MRI data are categorized as “positive” and “negative” at the joint/location level and at the patient level. In addition, MRI data obtained during follow-up will also be categorized as “positive” and “negative” at the joint/location level and subsequently at the patient level. Categorization in positive/negative will be done with MRI data of symptom-free persons as a reference [13], similar to the methodology used at inclusion.Immunological exploratory endpoints: signatures of immune responses (such as the presence/absence of ACPA and RF, characteristics of the ACPA response, and other post-translational modifications such as anti-carbamylated protein antibodies), levels of acute-phase reactants (erythrocyte sedimentation rate, CRP), and inflammatory responses as defined through the analysis of serum and peripheral blood cell subsets (RNA expression profiling) and proteomics.(Serious) adverse events ((S) AEs).

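### Scanner is corrected for only if at most 30 paired scans look different, so an undetected 1.5-T to 3-T shift can enter change from baseline on the exploratory MRI endpoint

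*Protocol article*

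**What the plan says.** The protocol article, under Plans for assessment and collection of outcomes {18a}, describes an amendment (protocol version 5) made because the 1.5-T scanner was expected to reach the end of its technical life after December 2019. Inclusion scans are foreseen to be complete by then. Follow-up scans may be on either machine, according to availability.

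To compare the machines, "we planned to perform both 1.5-T and 3-T MRIs in up to 30 participants". The comparison is of presence of inflammation per joint, bone or tendon sheath, and a two-branch rule follows:

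- If presence "will be similarly portrayed with both scanners, no further action will be needed".
- If 3-T is more or less sensitive, "a correction factor will be included in the analyses on the serial MRIs at the time of analyzing the results on this exploratory endpoint", with the factor derived from the same paired scans.

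On the number of pairs the text says: "The number of participants needed to scan on both machines is difficult to calculate". It then judges 30 sufficient, citing good comparability in the literature and mentioning that several locations come from one participant.

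MRIs are made at entry, at 4, 12 and 24 months, and when the primary endpoint is reached. Methods: outcomes {12} lists MRI among the explorative endpoints. It is analysed as a sum of graded scores for synovitis, bone marrow edema and tenosynovitis, and in addition "MRI data obtained during follow-up will also be categorized as" positive or negative against a symptom-free reference.

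**The concern.** The first branch treats failure to see a difference as proof that there is none. That inference needs a precise estimate, and at most 30 participants do not give one. Thirty is also a ceiling with no minimum.

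The check does not match the endpoint. Presence per location can agree on both machines while grades differ, and the rule would then apply no correction to the summed score.

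The layout of the scans makes this matter. With entry at 1.5-T and later visits on either machine, scanner is tied to visit and to calendar time. A shift left in the data would mix with change from baseline and with conversion between positive and negative status. Mixed scanners at one visit would also add variance to the arm comparison.

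**Working it through.** **1. The plan's own counts.** The plan states that "one scan depicts 12 small joints, 22 bones, and 18 tendon sheaths" and gives totals of "360 hand/foot joints, 660 bones, and 540 tendon sheaths". These reproduce: 30 × 12 = 360, 30 × 22 = 660, 30 × 18 = 540. No margin, power or confidence level is stated for the scanner comparison, so there is no further figure to reproduce.

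**2. Precision of a mean paired difference at participant level.** The 95% half-width is t(0.975, n−1)/√n, in SDs of the paired difference.

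| Pairs | Half-width |
|---|---|
| 30 | 2.045/√30 = 0.37 SD |
| 20 | 0.47 SD |
| 15 | 0.55 SD |

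No equivalence margin tighter than about 0.37 SD can be met with 30 pairs. This needs no assumed effect size.

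**3. Translation to the score scale (assumption).** The SD of a paired difference is √(2(1−ICC)) score SDs. The plan gives no between-scanner agreement. If the ICC were 0.90, the SD of the difference is √0.20 = 0.447, and 0.37 SD is about 0.17 score SD. If it were 0.70, √0.60 = 0.775, giving about 0.29 score SD.

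**4. Location-level comparison (illustration).** Many locations per scan do not restore precision once locations correlate. Effective N = 30m/(1 + (m−1)ρ), where m is locations per scan and ρ the within-participant correlation. For joints at ρ = 0.1 this is 360/2.1 = 171. Assume 5% of locations positive on 3-T only and 2% on 1.5-T only, with a two-sided 5% McNemar test:

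| Location | Power, ρ = 0 | ρ = 0.1 | ρ = 0.3 |
|---|---|---|---|
| Joints | 58% | 32% | 18% |
| Bones | 83% | 38% | 19% |
| Tendon sheaths | 75% | 36% | 18% |

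The plan gives neither ρ nor discordance rates.

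**5. Patient-level paired t-test (illustration).** With 30 pairs and two-sided 5%, power is 26% at a standardised difference of 0.25, 46% at 0.35 and 75% at 0.5. For 80% power the difference must be about 0.53. These effect sizes are assumed.

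**6. Possible share of 3-T scans by visit (illustration).** Trial status and other additional information gives first randomization in April 2015 and an expected end in September 2021. Subtracting 24 months puts last entry at about September 2019, 53 months after the start. Assume even accrual and a complete switch at the end of 2019, 56 months after the start. The share at visit month v is then (53 − (56 − v))/53 = (v − 3)/53:

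- Entry: 0%
- Month 4: 1/53 = 2%
- Month 12: 9/53 = 17%
- Month 24: 21/53 = 40%

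An uncorrected mean shift of size s would, on these assumptions, add about 0.02s, 0.17s and 0.40s to mean change from baseline at the three visits, in both arms.

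**The case against.** The plan foresaw the scanner change, arranged paired scans within a week of each other, and committed to a correction if sensitivity differs. The endpoint is exploratory, MRI results during the trial are not reported back, and the primary endpoint rests on physical examination alone. A scanner shift would appear in the placebo arm too. The choice of test and any margin could sit in the analysis plan, which is not shown. All of this stands and keeps the point small. What does not fall to the analysis plan is the instruction to do nothing when the scanners look alike: the protocol fixes that itself.

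A reader might infer that the treatment comparison is biased. The documents do not support this. Allocation is randomized and blinded, and scanner follows availability, so scanner use at a scheduled visit should be similar in both arms. The scan made at the primary endpoint is a partial exception, since its timing, and so possibly its scanner, could differ by arm.

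A reader might also infer that the plan overlooks clustering. It does not: it names clustering, though it gives no correlation.

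Nor can the 3-T shares or the 26–46% power be read as facts about the trial. The plan allows either machine throughout follow-up rather than a sharp switch, states no patient-level t-test, and does not define similarity by a p-value. Small missed shifts may also matter little. With a between-scanner ICC of 0.90, differences of 0.25–0.35 SD are 0.11–0.16 score SD; with 40% of month-24 scans on 3-T, that is about 0.05–0.06 score SD in the mean.

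Finally, adjusting always is not free. Outside the paired scans, the scanner effect is partly confounded with visit and calendar time.

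**Conclusion.** The point holds as a minor one. The rule lets at most 30 pairs that look alike switch off the scanner correction, although such a sample cannot exclude a mean shift smaller than about 0.37 SD of the paired difference. It also tests presence when the endpoint includes grades. What is exposed is within-participant change from baseline, follow-up positive/negative status, and precision.

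The 0.37 SD figure depends only on 30 pairs and a 95% interval; fewer pairs make it worse. The sizes in score units, the power figures and the 3-T shares are illustrations on assumptions the document does not give. Whether the two scanners differ at all cannot be told from it. An apparent rise in inflammation after tablets stop is therefore a possible misreading to guard against, not a predicted result.

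**What to change.** Replace the two-branch rule. Include the field strength of each scan as a term in every serial-MRI model, whatever the paired comparison shows. Keep the paired scans in the model with a participant random effect so that they inform the scanner effect. Do this for the graded summed score as well as for presence.

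An analysis restricted to 1.5-T scans can be added as an optional sensitivity check. It would drop later-enrolled participants, so it should not carry the conclusion.

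No new scans or visits are needed, but the machine used must be recorded for each scan. The cost is some precision, and somewhat more than one degree of freedom suggests, because the scanner effect rests largely on few pairs. If it came from 30 pairs alone and 40% of month-24 scans were at 3-T, its uncertainty would contribute a 95% half-width of about 0.40 × 0.37 = 0.15 SD of the paired difference to mean within-arm change at month 24. The comparison between arms would lose much less.

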### Plans to promote participant retention and complete follow-up {18b}

The intention is to follow all participants for a total period of 24 months of the RCT at the LUMC. Participants who need to stop the study medication because of toxicity (or other reasons, e.g., wish of participant) will remain in the trial for the entire follow-up period. In case a participant finds the trial too demanding, we will ask if an adjusted scheme is an option, which will at least include the last visit at the LUMC at 24 months, and if also possible the 12-month visit.

Participants who will reach the primary endpoint will be treated by their rheumatologist according to the Dutch and international guidelines. Participants who reach the primary endpoint will be asked to complete the questionnaires at month 24.

Amendment (Protocol version 7, 25-02-2020) includes the collection of observation data between 24 and 60 months and questionnaires completed by the participants at 5 years of follow-up. All included participants will be contacted 5 years after the inclusion in the cohort to complete the questionnaires at month 60. Data from the disease course between months 24 and 60 will be retrieved from the medical files if participants consent with the observational extension study. This extension phase is submitted to and approved by the medical ethical testing committee (METC) in 2020, partly in response to comments of patient partners that suggested to determine if differences between the groups will be sustainable in the long term.

### Data management {19} and confidentiality {27}

All participant data gathered at planned and unscheduled visits will be stored and handled within the LUMC, Department of Rheumatology, in an electronic data capture (EDC) platform (ProMISe; NEN7510 certificated based on ISO27001) hosted on a dedicated secure website by the LUMC. The advanced data management (ADM) team has extensive experience with this system. Password, two-step verification management, and data exports will be controlled by the ADM team. Changes to the EDC system once the trial has begun will be minimized and will be undertaken only with the full agreement of the principal investigator, study coordinator, and the METC that is essential to the successful conduct of the study.

Participants who consent to the screening but who are subsequently found to be ineligible will also be recorded in the EDC system for “Consolidated Standards of Reporting Trials” (CONSORT) reporting purposes. These procedures will operate in accordance with the guidelines for GCP, meeting the requirements of the medicines and healthcare products regulatory agency.

Participant data will be stored under randomization number, conform to GCP guidelines. Research nurses will enter trial data in this platform, which contains study assessment data, including physical examination by a research nurse and physician data, routine lab data, (S) AE and intermittent (co)morbidities) information, and questionnaires data. The study doctor will monitor the entered data, which is a first QC, and will verify the data, checking medical forms to assure that participants have not met the endpoint and have not received concomitant medication other than NSAIDs. In addition, the study doctor will check if all (S) AEs are reported. A second QC will be performed by the study coordinator that includes all previous checks as mentioned for the study doctor. Next, the EDC system can lock every participant and every study visit, which is done by the study coordinator after approval of the principal investigator, conform to GCP guidelines.

Before unblinding (last study visit at 2 years of follow-up of the last included participant), the EDC platform will be completely locked by the ADM team under the supervision of the principal investigator. Thereafter, unblinding will take place, and the first analyses will be performed according to the statistical analysis plan.

The data manager (LUMC, Department of Rheumatology) will supervise the entire process and keep the original participant clinical forms/information/data and body material (blood) stored for at least 20 years after the last study visit of the last included participant. The ADM team, data manager, and principal investigator directly involved in this trial will be authorized to access the database but will always be blinded during the trial. In addition, QC of the data can also be performed by monitors (employees of LUMC or hired by the LUMC) and/or Dutch authorities.

All reasonable precautions to maintain the confidentiality of participants’ identities and protect the integrity of the data will be taken.

### Plans for collection, laboratory evaluation, and storage of biological specimens for genetic or molecular analysis in this trial/future use {33}

Blood samples will be processed, frozen, and stored anonymously (by randomization number) at − 80 °C locally in the LUMC for later usage. This concerns DNA, RNA, serum, and plasma. An explorative endpoint, as described in the “Outcomes {12}” section, is analyzing the signatures of immune responses and inflammatory responses.

## Statistical methods

### Statistical methods for primary and secondary outcomes {20a}

All statistical methods for the primary and secondary endpoints will be described in the statistical analysis plan, which will be completed and submitted before unblinding. Analyses will be based on the intention-to-treat (ITT) and per-protocol (PP) population. The ITT population will consist of all participants randomly assigned to a treatment group. The ITT population will form the primary analysis population of the trial and will be used for all primary and secondary efficacy endpoints and for safety analyses. This strategy is conservative because it tends to underestimate the difference in the outcome between the treatment groups, but it respects the randomization process, is free from bias, and resembles clinical practice. The PP population will consist of all participants meeting the study entry criteria, who completed follow-up and who in the first year after randomization, or up to a primary event in this period, have used ≥ 8 study tablets a week (equivalent to at least 20 mg/week MTX) for 80% of the time and used no forbidden medication (no systemic or intra-articular steroids or DMARDs outside the study protocol) during the entire follow-up period. An MTX dose of ≥ 20 mg/week has been shown to provide optimal efficacy in RA [31, 32, 34]; therefore, a dose of ≥ 8 study tablets was incorporated in the definition. The PP population will consist of participants who strictly adhere to the protocol and provide an estimate of the true efficacy of the MTX intervention. All primary and secondary efficacy endpoints will also be analyzed in the PP population. The primary analysis will be the time to the development of the primary endpoint. The co-primary endpoint is the difference in the percentage of patients that achieved DMARD-free status at 24 months. Significance will be assessed by a gate-keeping analysis. We do prioritize the two primary endpoints by testing the primary endpoint first, and only if this test is significant, the co-primary endpoint will be tested.

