### Intervention description {11a}

In this double-blind RCT, participants will be randomized to two arms in an 1:1 ratio. The randomization consists of one IM glucocorticoid injection (120 mg methylprednisolone or IM placebo injection) followed by 12 months of MTX tablets (or placebo tablets) (Fig. 2). No other corticosteroid interventions will be allowed during the trial, unless participants have reached the primary endpoint and proceeded to open-label DMARD therapy.

MTX (or placebo) tablets will be increased in 4 weeks to 10 tablets/week (25 mg/week). Open-label folic acid supplementation (5 mg/week) will be added, in line with the Dutch guidelines of MTX use (https://www.nvr.nl/richtlijnen/nvr-richtlijnen-standpunten-en-zorgpaden/). After 45 weeks of 10 tablets/week (MTX or placebo), tablets will be tapered for 4 weeks and then stopped at week 53. Participants will be followed for another 12 months.

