The follow-up duration of 24 months seems sufficient for the assessment for the primary endpoint, because our present data suggest that the majority of CSA patients who convert to clinically detectable arthritis and RA do so within 4–6 months [14]. The follow-up includes 12 months without study medication. Supposed that MTX would postpone but not prevent the development of RA, a medication-free period of 12 months should be sufficient to detect this. Also, in the PROMPT trial, only two patients developed RA later than 12 months after cessation of study medication [48]. Nonetheless, the most recently approved amendment to the protocol (approved February 2020, protocol version 7) includes an observational extension of the trial with a total follow-up time of 5 years, as the achievement of an outcome after a relatively short time period of time is not reflective of the subsequent disease course [49]. A long-term follow-up is required to evaluate whether results are sustainable and valuable. Especially, patients have indicated that the current disease burden is mostly caused by pain, fatigue, and functional impairments [50]; the decision to extend the follow-up duration is therefore in line with the suggestions of patient partners. After 5 years follow-up, we will assess primary and secondary endpoints, to evaluate if differences are permanent in the longer term.

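### The per-protocol adherence rule counts escalation weeks as shortfall, so a fully adherent participant can be excluded solely because the primary event came early

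*Protocol article*

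**What the plan says.** Section {20a} of the protocol article states the PP rule in full. Besides meeting the entry criteria and taking no forbidden medication, PP participants are those "who completed follow-up and who in the first year after randomization, or up to a primary event in this period, have used" at least 8 study tablets a week ("equivalent to at least 20 mg/week MTX) for 80% of the time"). The adherence window thus runs from randomization to one year, or to the primary event if that comes sooner. Nothing is said about weeks in which the schedule itself prescribes fewer than 8 tablets.

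Such weeks can occur at both ends of the schedule in Intervention description {11a}. At the start, "MTX (or placebo) tablets will be increased in 4 weeks to 10 tablets/week (25 mg/week"). At the end, "After 45 weeks of 10 tablets/week (MTX or placebo), tablets will be tapered for 4 weeks and then stopped at week 53". The weekly steps are not given.

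The purpose of the set is also in {20a}: "The PP population will consist of participants who strictly adhere to the protocol and provide an estimate of the true efficacy of the MTX intervention". Every efficacy analysis, whether primary or secondary, is to be repeated in it, and the primary analysis is time to event. Intention-to-treat (ITT) is the primary population.

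On timing, the Discussion says that "the majority of CSA patients who convert to clinically detectable arthritis and RA do so within 4–6 months".

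**The concern.** Adherence is a proportion of elapsed time, and an early event shortens that time. The escalation weeks are fixed at the start, so the shorter the window, the larger the share they take up. Two participants who both follow the schedule exactly can then be classified differently, and the only difference between them is when, or whether, the event occurred.

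This is selection on the outcome. Everyone left in the PP set is event-free by construction over the first weeks, so a time-to-event analysis started at randomization contains a stretch in which no PP participant can have an event. The arm with more early events also loses more participants. A set built this way does not match its description as strict adherers who show the true efficacy.

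**Working it through.** **Inputs**
- Window and threshold: section {20a}, as above.
- Schedule ({11a}): 4 weeks of escalation, 45 weeks at 10 tablets, 4 weeks of taper. 4 + 45 + 4 = 53, which matches the stated stop at week 53.
- k = escalation weeks below 8 tablets: not stated. Assumed range 1 to 4.
- First scheduled visit: month 4, week 17.33. Persistence is checked 2 weeks later, week 19.33 ({11d}, {18a}). Unscheduled visits are possible when symptoms increase ({11d}).
- Planning rates ({14}): 35% in controls and a 50% reduction, so 35% vs 17.5%, with 115 per arm.

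**Step 1: score of a perfect adherer with an event at week T**

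Score = (T - k)/T = 1 - k/T. The rule needs 1 - k/T ≥ 0.80, that is T ≥ 5k.

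| k | Excluded if event before | Score at week 17.33 | Score at week 19.33 | Score at week 26 |
|---|---|---|---|---|
| 1 | week 5 | 94.2% | 94.8% | 96.2% |
| 2 | week 10 | 88.5% | 89.7% | 92.3% |
| 3 | week 15 | 82.7% | 84.5% | 88.5% |
| 4 | week 20 | 76.9% | 79.3% | 84.6% |

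**Step 2: score of a perfect adherer with no first-year event**

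Even if every escalation and taper week is below 8 tablets, the score is 45/53 = 84.9% (or 45/52 = 86.5%). This participant always passes.

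**Step 3: slightly imperfect adherence**

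With k = 3 and one missed week, an event at month 4 scores (17.33 - 4)/17.33 = 76.9% and fails, although 13.33/14.33 = 93% of the post-escalation weeks were taken.

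**Step 4: share of events before the cut-off**

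The documents give no event-time distribution. As an assumption, take an exponential truncated at 104 weeks: share(t) = (1 - exp(-λt))/(1 - exp(-104λ)). Set λ so that 51% of events fall by month 6 (λ = 0.0244 per week) or by month 4 (λ = 0.0403 per week), with the same shape in both arms. Planned events: 115 × 0.35 + 115 × 0.175 = 40.25 + 20.13 ≈ 60.

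| k | Cut-off | Share of events lost | Events lost of about 60 |
|---|---|---|---|
| 1 | week 5 | 13-19% | 8-11 |
| 2 | week 10 | 24-34% | 14-20 |
| 3 | week 15 | 33-46% | 20-28 |
| 4 | week 20 | 42-56% | 25-34 |

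A steeper assumption, 80% of events by month 6, gives 27%, 46%, 60% and 71%.

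**Step 5: effect on the estimate**

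Removing a share s of events in each arm turns a rate p into p(1 - s)/(1 - ps).
- s = 0.125: 32.0% vs 15.7%, risk ratio 0.49, difference 16.4 points.
- s = 0.561: 19.1% vs 8.5%, risk ratio 0.45, difference 10.6 points.
- No exclusion: 35% vs 17.5%, risk ratio 0.50, difference 17.5 points.

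On a hazard scale, ln(1 - p_treated)/ln(1 - p_control) moves from 0.447 to 0.441 and 0.420 respectively. The relative effect hardly moves; the number of events does.

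**The case against.** **The size rests on a titration that the article does not state.** Only weeks below 8 tablets count, and {11a} gives no steps. This stands. A reader might infer that events found at the month-4 visit are always excluded, or that the PP set is conditional on about five event-free months. Under full adherence both are true only for k = 4.

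**Timing.** A reader might also infer that the rule deletes the period in which most events lie. The documents do not support that. Conversion mostly within 4 to 6 months means by weeks 17 to 26, and at week 26 every full adherer passes whatever k is. With k of 3 or less, a full adherer is lost only if the event is found at an unscheduled visit before the month-4 visit, and the article gives no frequency for those. The continuous-time shares above may therefore be too high.

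**The relative effect is nearly unchanged.** This stands if event timing has the same shape in both arms. It need not hold if the treatment acts mainly in the excluded weeks.

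**PP is secondary, and handling of non-adherence is deferred to the analysis plan.** The first part stands and limits the severity. The second does not remove the point: {20a} already fixes the window, the dose and the 80%. The unseen plan may clarify how escalation is counted.

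**Other features of the rule are not errors.** Dropping participants on a reduced dose is deliberate, and the article justifies the 8-tablet level. Requiring completed follow-up is a common PP criterion. That the 80% threshold is strict for event-free participants is a design choice, since a perfect adherer still passes. No figure shows that dose reductions fall mainly in the methotrexate arm.

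**Conclusion.** The point holds as a fault in a stated rule. Read literally, the PP definition excludes participants who follow the schedule exactly when their event comes before week 5k, and includes equally adherent participants without a first-year event. That conflicts with the purpose the article gives for the set.

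The mechanism needs only one escalation week below 8 tablets. The size is uncertain: from about one eighth to over one half of events, depending on k and on an assumed event-time distribution. The consequence is lost early events and lower precision in the PP analysis, plus a description of that analysis that is too strong. The primary ITT result is untouched. Severity is minor to moderate; this is not a must-fix.

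**What to change.** Amend the PP definition before unblinding so that adherence is measured against the scheduled regimen. Either form works:
- tablets taken divided by tablets scheduled, up to one year or the event, at least 80%; or
- at least 8 tablets a week in at least 80% of the scheduled full-dose weeks, counted up to the event or the start of the taper.

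State that otherwise adherent participants whose event occurs during or soon after escalation stay in the set. The second form needs this explicitly, because an event before the first full-dose week leaves no weeks to count. With either form a perfect adherer scores 100% or is retained by this rule, whatever the event time.

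Describe the PP analysis as supportive rather than as the true efficacy.

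The cost is one reworded definition. The medication diaries in {11c} already collect the data, and neither sample size nor conduct changes. After unblinding, the same change could look data-driven.
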